### Medication and health service use

Medication and health service use will be measured at baseline, posttreatment and follow-up for all patients. They will be measured using the pain version of the Client Service Receipt Inventory (CSRI) [31]. This will provide information on medication and health service resource use. The CSRI has been used widely in economic cost-of-illness studies, including studies of chronic pain [5,32,33], and has been validated as an accurate measure of frequency of health service use [34]. Medication use is likely to vary throughout the trial duration, and GPs will be allowed to vary medication as they see fit. However, change in medication use will be measured in post-treatment analysis. In cases of potential dual-use medication being taken by a patient, we will, with the patient’s consent, confirm with the prescribing GP if the medication was prescribed for pain or otherwise. Additional information will be gathered on (1) demographic variables (age, education, marital status); (2) pain-related information (duration of pain, number of pain sites, recurrence of pain, previous attendance at a pain management programme); and (3) details of any comorbid health conditions.

A patient is deemed suitable to go forward to the treatment allocation stage of the trial based on the presence of elevated psychosocial risk factors. This is defined as a score above the 50th percentile on any of the five risk factors targeted by the intervention: catastrophizing (Pain Catastrophizing Scale), fear of movement (Fear-Avoidance Beliefs Questionnaire), disability (Roland-Morris Disability Questionnaire), depression (Hospital Anxiety and Depression Scale) and fatigue (Fear and Fatigue Scale).

### Randomisation and treatment allocation

Eligible participants (that is, those who show elevated psychosocial risk factors) will be randomly assigned by computer-generated block randomisation to ‘intervention’ (PGAP sessions plus MTAU) or ‘control’ (MTAU only). We expect 20 participants to take part in the trial in each of the seven trial centres. Therefore, block randomisation with variable block sizes is used to minimize the occurrence of chance imbalance in allocation to treatment and control and to preserve unpredictability. The sequence of the different blocks is predetermined by an independent researcher not involved in the trial and concealed to all investigators. The blocks are generated separately for the different study sites so that stratification according to trial centre can be performed. It was decided to stratify on trial centre only for pragmatic reasons. Stratifying on additional variables, although useful, would have called for a larger sample. As each treating psychologist was seeing these trial patients in addition to their usual caseload, a limit was placed on the number of patients each clinician would be asked to see, thus limiting stratification.

### Progressive Goal Attainment Program

The PGAP is a 10-week one-to-one rehabilitation programme delivered in this trial by clinical psychologists. Each session is 1 hour long. The intervention was specifically designed to assist those individuals with thought patterns and behaviours which are known to increase risk for chronic disability. Patients are offered a maximum of 10 individual appointments with the PGAP psychologist. At their first appointment, patients receive an instructional DVD which orientates them to the PGAP and explains the importance of activity mobilization. Through the course of the treatment programme, the PGAP clinician assists the patient in identifying ways to increase activity involvement. Working with the PGAP clinician, the patient develops an activity schedule that is designed to keep him or her as active as possible. This may include household activities, running errands and social and recreational activities. A central element is a programme of regular walking. The patient’s spouse or partner is invited to participate in activity planning so that he or she is aware of the program that is being developed for the patient.

In the second phase of the program, the patient develops skills to overcome fears of reinjury and learns to monitor and modify self-defeating thinking that may accompany pain. The patient is taught methods of approaching physical activity in a way that minimizes worries and concerns about potential reinjury by using cognitive behavioural therapy strategies. Specifically, the programme addresses functional activity scheduling, activity pacing and psychological obstacles to progress such as fear of movement and reinjury, pain catastrophizing and the impact of negative or pessimistic thinking on emotional well-being and activity level. Finally, the patient learns communication skills and problem-solving strategies that will assist him or her in meeting the challenges brought on by the injury.

A total of 11 clinical psychologists employed in the public health service were trained to deliver the PGAP. This training involved attending a 2-day workshop delivered by the developer of the intervention ([name], McGill University, Montreal, QC, Canada). The psychologists involved in the trial are spread geographically throughout the Republic of Ireland and will see patients as part of this trial in their usual clinics.

Patients who have been randomly assigned to the intervention condition are contacted by the researcher involved in the trial to discuss their participation. An appointment is arranged with a PGAP psychologist who is geographically closest to the patient. Each patient is seen for a maximum of 10 hourlong one-to-one appointments with the PGAP psychologist. In parallel with these sessions, patients are free to access their GP and any other healthcare professional as usual. Patients are offered a maximum of 10 sessions with the clinical psychologist as part of the PGAP. Each patient is given a copy of the *Client Manual*, a workbook of exercises to be completed as part of the programme. The programme may be terminated earlier if the patient is able to return to work before attending all 10 sessions. Termination of treatment before the end of the 10 sessions will be at the discretion of each psychologist in consultation with the patient and patient’s GP.

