### Sample size

Following published guidelines [22], the sample size calculation was based on having 80% power at the 5% significance level to detect a difference in mean post-treatment improvement of 3 units or more on the Roland-Morris Back Pain Questionnaire between the control and intervention groups, assuming that the standard deviation of the improvement is 6.1 units in both groups [14]. In order to ensure sufficient power to detect such a difference, a sample size of 60 is needed for each arm. However, allowing for an attrition rate of 15% [16], and based on the experience of [name] *et al*. (personal communication [name], September 2007), we aim to include 140 participants (70 per group) in the study and expect to have complete data for about 120 participants following dropouts.

Screening of larger numbers of patients will be required to obtain a sample of 140. On the basis of recent research examining the prevalence of psychosocial risk factors among a general practice population, where at least one factor was found in 24% of respondents and up to 52% had a particular risk indicator, we expect that 20% to 50% of our sample frame will have one or more of the psychosocial risk factors [23].

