### Quantitative analysis

Patients participating in the PGAP trial are heterogeneous in terms of specific back pain problems, length of time in pain, history of attending pain management programmes and current medical management, including medication. Therefore, participating patients’ age, gender, marital status, length of time in pain, medical diagnosis (if any), number of pain sites, previous medical or therapeutic procedures and current medication is be gathered as potentially useful explanatory variables in all analyses.

The longitudinal change in the response variables of interest across treatment arms will be analysed using a linear mixed model to compare the change within individual participants (that is, before and after the intervention) and between the study arms (that is, comparing the cohort of patients who received the PGAP intervention to the control group participants), adjusting for baseline, treatment centre and patient characteristics as necessary. It will be assumed that missing data are missing at random, and the sensitivity to this assumption will be assessed using multiple imputations based on chained equations [35].

The selection of explanatory variables for inclusion in all final models will be based on a combination of clustering, tree-based methods and variable selection techniques applied to the complete cases and to the imputed data. All analyses will be carried out using R software [36] and SPSS software (SPSS Inc, Chicago, IL, USA) as necessary.

Model-checking will be performed using suitable model diagnostics and residual plots. Sensitivity analysis will be used to explore whether adherence to the intervention influences the effect of the intervention on the primary outcome.

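### The stated model has no term for the treating psychologist, who exists only in the PGAP arm; if the psychologist ICC is above 0, the standard error is understated even after centre adjustment

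*Protocol article*

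**What the plan says.** The section on the Progressive Goal Attainment Program describes individual hour-long sessions, up to ten per patient, and states: "A total of 11 clinical psychologists employed in the public health service were trained to deliver the PGAP". Patients are not randomised to a psychologist: "An appointment is arranged with a PGAP psychologist who is geographically closest to the patient". Treatment may end early at the psychologist's discretion, after consulting the patient and GP. Under Control condition, control patients do not receive PGAP, so they have no trial psychologist.

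Randomisation is stratified by centre, with about 20 patients expected in each of seven centres. The same section says that each clinician's caseload was capped, without giving the cap.

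Under Quantitative analysis, the response variables are compared between arms with a linear mixed model, "adjusting for baseline, treatment centre and patient characteristics as necessary". The treating psychologist is not in that list.

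The Sample size section asks for "80% power at the 5% significance level" "to detect a difference in mean post-treatment improvement of 3 units or more", "assuming that the standard deviation of the improvement is 6.1 units in both groups", and concludes that "a sample size of 60 is needed for each arm". It mentions no ICC and no design effect.

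**The concern.** The design is partially nested. Each PGAP patient belongs to a psychologist's caseload, and each control patient stands alone. Patients of one psychologist may have similar outcomes because they share that clinician's skill, style and decisions on when to stop. If so, the PGAP arm mean carries an extra variance component that shrinks with the number of psychologists rather than the number of patients.

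A centre term does not remove it. A centre main effect moves both arms by the same amount, while a psychologist effect moves only the PGAP patients. Even with exactly one psychologist per centre, the psychologist effect would be a centre-by-arm interaction, and the stated list contains no such term.

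Two things are at stake. The confidence interval for the primary comparison may be too narrow, with a type I error above 5%. The analysis would also not show whether benefit varies between psychologists. That matters for a pragmatic trial whose stated aims include the feasibility and effectiveness of a community-based programme.

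**Working it through.** **Inputs from the protocol article.** Difference 3, SD 6.1, 80% power, 5% level, 60 analysed per arm (Sample size); 11 psychologists trained (Progressive Goal Attainment Program); seven centres (Randomisation and treatment allocation).

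**Assumptions.** The test is two-sided. All 11 psychologists treat equal numbers. The psychologist ICC, ρ, lies between 0.01 and 0.10. The documents give neither the ICC nor the caseloads.

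**The plan's own figure, without clustering.**

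n per arm = 2 × [6.1 × (1.960 + 0.842) / 3]² = 64.9, so 65 rather than 60.

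At 60 per arm, SE = 6.1 × √(2/60) = 1.114, and power = Φ(3/1.114 − 1.960) = 76.8%. A t-based calculation gives 66 per arm and 76.2%. A one-sided test would need 52 per arm. The baseline for judging clustering is therefore 76.8%, not the nominal 80%.

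**Adding psychologists in one arm.**

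- Patients per psychologist: m = 60/11 = 5.45
- PGAP-arm design effect: DE = 1 + (m − 1)ρ
- True SE divided by reported SE: r = √[(1 + DE)/2]
- Type I error of the unadjusted test: 2 × [1 − Φ(1.960/r)]
- Power once the SE is right: Φ(3/(1.114 r) − 1.960)

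For ρ = 0.05: DE = 1 + 4.45 × 0.05 = 1.223, and r = √(2.223/2) = 1.054. Type I error = 2 × [1 − Φ(1.859)] = 6.3%. Power = Φ(3/1.174 − 1.960) = 72.4%.

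| Assumed ICC | DE | SE ratio | Type I error | Power at 60 per arm | Points lost from 76.8% |
|---|---|---|---|---|---|
| 0 | 1.000 | 1.000 | 5.0% | 76.8% | 0 |
| 0.01 | 1.045 | 1.011 | 5.3% | 75.9% | 0.9 |
| 0.02 | 1.089 | 1.022 | 5.5% | 75.0% | 1.8 |
| 0.05 | 1.223 | 1.054 | 6.3% | 72.4% | 4.4 |
| 0.10 | 1.445 | 1.106 | 7.6% | 68.3% | 8.5 |

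**Does centre adjustment repair it?** This was checked by simulation: 40,000 trials per setting, 120 patients, seven centres, 11 psychologists (two in four centres, one in three), with centre fitted as a fixed effect. With no centre variance, the empirical SD of the treatment estimate divided by the mean model SE was 1.00 at ICC 0. At ICC 0.01, 0.02, 0.05 and 0.10 it was 1.02, 1.03, 1.06 and 1.13, with type I error of 5.3%, 5.6%, 6.5% and 8.0%. Adding a centre ICC of 0.05 left these nearly unchanged. Centre adjustment does not help, and the formula above slightly understates the problem.

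**If fewer psychologists treated patients.** With seven, m = 60/7 = 8.57. At ICC 0.02, 0.05 and 0.10 the SE ratio becomes 1.037, 1.091 and 1.174, type I error 5.9%, 7.2% and 9.5%, and power 73.8%, 69.5% and 63.1%.

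**The case against.** The strongest objection is one of standing. This is a condensed article, the SAP is not shown, and random-effects structure is commonly left to it. A reader might infer that the sponsor decided to leave psychologists out of the model. The text does not support that: the adjustment list ends with a qualifier of necessity, and nothing rules a psychologist term out. The point still stands in a narrower form. The article names its model and its adjustment set, and gives a full sample-size calculation. An analyst who followed that text would omit the one level of clustering that the design creates.

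A second objection is size. The programme is manual-driven, with a shared two-day training workshop, a DVD and a patient workbook, all of which may limit differences between psychologists. At an ICC of 0.01 or 0.02 the understatement is only 1% to 3%. This is fair, but those features do not show that the ICC is zero.

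A third objection is that a variance component from at most 11 clusters of about five patients will be imprecise and may be estimated at zero. Because patients go to the nearest psychologist, it also mixes psychologist with locality. That stands. It limits what the estimated ICC can say about individual psychologists and makes a prespecified sensitivity analysis a defensible minimum.

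**Conclusion.** The concern holds conditionally. The stated model omits a level of clustering confined to the PGAP arm, and centre adjustment cannot absorb it. Whenever the psychologist ICC exceeds 0, the SE is understated. The size is small to moderate: about 2%, 5% and 11% at assumed ICCs of 0.02, 0.05 and 0.10, with 60 PGAP patients spread evenly over 11 psychologists. Fewer treating psychologists would make it larger.

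Four stronger readings are tempting and not supported:

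- **That the SE is certainly too small.** This needs an ICC above 0, and the documents give none.
- **That the model adjusts only for centre.** Baseline and patient characteristics are also listed, though neither stands in for the psychologist.
- **That 11 psychologists treated patients.** Eleven were trained; how many saw trial patients, and how many patients each saw, is not stated.
- **That clustering explains the whole gap from 80% power.** Power is already 76.8% with no clustering, because 60 per arm does not follow from the stated difference and SD. Clustering itself costs about 2, 4 and 8 points (1.8, 4.4 and 8.5) at ICCs of 0.02, 0.05 and 0.10.

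**What to change.** Record the treating psychologist for every PGAP patient. The trial researcher contacts these patients and an appointment with a named psychologist is arranged, so this should need no new data collection.

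Fit the primary mixed model as partially nested: a psychologist random effect in the PGAP arm only, each control as a cluster of one, Satterthwaite or Kenward-Roger degrees of freedom, and randomisation centre kept as the stratification term. If the sponsor prefers the stated model as primary, prespecify the partially nested model as a sensitivity analysis at minimum.

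Report the psychologist variance component or ICC with its interval, the number of psychologists who treated patients and their caseloads. Say that the estimate is imprecise and partly mixed with locality. If the SAP already contains such a term, bring the protocol description into line with it.

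The article reports recruitment complete in May 2013, so the remedy lies in the analysis rather than the sample size. For the record, with 11 psychologists the analysed number per arm would solve (2 − ρ)/n + ρ/11 = [3/(6.1 × 2.802)]². This gives 69, 75 and 88 at ICCs of 0.02, 0.05 and 0.10, against 65 without clustering.

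The cost is one extra random term, a slightly wider interval, and a variance component that rests on at most 11 clusters.

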### Control condition

Patients allocated to the control condition do not receive the PGAP. The patient is contacted by the researcher to explain that they have been allocated to the control condition and what this means. This gives the patient an opportunity to ask questions. This step is followed by written confirmation of the patient’s allocation to the control group. Patients in the control condition are free to access all healthcare services as usual. Patients who are randomised to the control condition will not be precluded from enrolling in a psychological pain management programme for the duration of this trial. If this happens, however, their data will be excluded from analysis. Participants in the control condition are sent assessment measures at baseline and at 10 weeks postbaseline. It is recognized that GP care will vary from individual to individual.

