## Methods and design

This PGAP study is a pragmatic, multicentre randomised controlled trial of a cognitive behavioural therapy–based active rehabilitation programme for patients who are work-disabled due to back pain.

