#### Exclusion criteria

Patients are not eligible to participate in the trial if they meet any of the following exclusion criteria. (1) The GP confirms the presence of ‘red flags’ indicating serious pathology (for example, cancer, fracture, infection). (2) The patient has serious cognitive and psychiatric comorbidity. This criterion will include patients who have a diagnosis of a serious axis 1 or axis 2 mental health disorder as defined by the *Diagnostic and Statistical Manual of Mental Disorders, Fourth Edition* (DSM-IV). (3) The patient has a cognitive impairment that may affect the ability to engage in the programme (for example, Alzheimer disease, aphasia, stroke). The presence of these conditions will be confirmed by the patient’s GP. (4) The patient is currently receiving psychological management for pain. (5) The patient is involved in litigation in relation to the injury.

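### Control patients who join a psychological pain programme after randomisation are excluded from analysis, which opens the primary comparison to selection bias of unknown direction

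*Protocol article*

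**What the plan says.** The Control condition section of the protocol article first leaves usual access open: "Patients in the control condition are free to access all healthcare services as usual". It then states, in a sentence that closes by naming the trial: "Patients who are randomised to the control condition will not be precluded from enrolling in a psychological pain management programme for the duration of this". The next sentence sets the consequence: "If this happens, however, their data will be excluded from analysis". No particular analysis is named, so as written the rule covers the primary, secondary and economic analyses alike.

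For the intervention arm, the Progressive Goal Attainment Program section says: "In parallel with these sessions, patients are free to access their GP and any other healthcare professional as usual". It attaches no exclusion to that freedom.

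Three other statements bear on the point:
- The Exclusion criteria list "The patient is currently receiving psychological management for pain", which is an entry condition for both arms.
- Quantitative analysis describes the between-arm contrast as "comparing the cohort of patients who received the PGAP intervention to the control group participants". The article contains no intention-to-treat statement.
- The trial describes itself in these terms: "This PGAP study is a pragmatic, multicentre randomised controlled trial".

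**The concern.** Randomisation makes the arms comparable at allocation. Removing patients for something they did afterwards, in one arm only, can undo that. Controls are told their allocation, and that knowledge may itself prompt some of them to look for another programme.

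Who looks is unlikely to be unrelated to outcome. If controls who enrol are those getting worse, deleting them improves the control mean and understates the benefit of PGAP. If they are the more motivated, or gain from the other programme, deleting them lowers the control mean and overstates it. The document does not allow the sign to be predicted.

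Timing makes this worse. The permission, and so the exclusion, runs for the whole trial, with follow-up at 12 months, while the primary outcome for controls is taken at 10 weeks. Read literally, a control who enrols some months after the 10-week questionnaire loses a primary outcome that the other programme could not have affected. Guarding against contamination cannot justify that.

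**Working it through.** **Does another part of the plan cure the rule?**
- The entry criterion on current psychological management acts before randomisation and does not reach later enrolment.
- Quantitative analysis states: "It will be assumed that missing data are missing at random", with multiple imputation as a sensitivity check. That concerns data that were not obtained. Here data may be in hand and are removed by rule. Imputing these patients from the retained controls would answer a different question, namely the outcome without the other programme.
- The planned sensitivity analysis on treatment received concerns adherence to PGAP. It does not restore the excluded controls.

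Nothing cures it.

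**Size of the shift.** The plan gives no figure for this exclusion, so there is none to reproduce. Let a share f of controls be excluded, with mean change m − g, and let the rest have mean change m.
- Mean of all controls: (1 − f)m + f(m − g) = m − fg.
- Mean of retained controls: m.
- Shift caused by the rule: f × g, with the sign of g.

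Inputs: 60 controls with complete data and a target difference of 3 units (Sample size section). Both f and g are assumptions. The last column is the larger shift divided by 3.

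| Controls excluded, of 60 (f) | Shift, g = 2 | Shift, g = 4 | Larger shift as % of target |
|---|---|---|---|
| 1 (1.7%) | 0.03 | 0.07 | 2% |
| 2 (3.3%) | 0.07 | 0.13 | 4% |
| 3 (5%) | 0.10 | 0.20 | 7% |
| 6 (10%) | 0.20 | 0.40 | 13% |
| 9 (15%) | 0.30 | 0.60 | 20% |

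As a guide to the effect on inference, f = 10% and g = 3 give a shift of 0.30 points. With 60 against 54 patients the standard error is 6.1 × √(1/60 + 1/54) = 1.144, and the two-sided type I error rises from 5% to about 5.8%.

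**Power lost through fewer controls.** Power = Φ(3/SE − 1.96), with SE = 6.1 × √(1/60 + 1/n_c), taking the test as two-sided (the article does not state sidedness).
- n_c = 60: 76.8%
- n_c = 57 (f = 5%): 75.8%
- n_c = 54 (f = 10%): 74.6%
- n_c = 51 (f = 15%): SE = 1.162, 3/1.162 − 1.96 = 0.62, power 73.3%

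The loss due to this rule is about 1 to 4 percentage points. The starting value of 76.8% rather than the stated 80% is a separate sample-size matter; this point does not rest on it.

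**The case against.** The strongest reply is that the rule will hardly ever be used. The Background section says that psychologically informed services for back pain are very hard to reach in the Irish community and that other community pain management services barely exist. One or two exclusions among 60 controls would move the estimate by 0.13 points at most under the gaps assumed here, and none would move it not at all. This stands as an argument about size. It does not make the rule sound, since the exposure window is the whole trial and the article gives no count. Scarcity also means that keeping these patients costs almost nothing.

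A second reply is that the Control condition section itself mentions only baseline and 10-week questionnaires for controls, so the trial's duration might be read as ending there. The Abstract and the Screening measures section, however, list the 12-month follow-up without restricting it to one arm.

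Third, the comparator is called usual medical treatment, so one can dispute whether another psychological programme belongs to it. The wording on free access to all services points the other way. The text is mixed, and the objection to post-randomisation exclusion does not depend on settling it.

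A reader might also infer more than the documents support:
- That PGAP patients who enter another programme are kept in the analysis. The article is silent; it can only be said that no matching rule is stated for them.
- That the rule removes the most expensive usual-care patients. Nothing in the article ranks them by cost.

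**Conclusion.** The rule is wrong as written. It is an unqualified post-randomisation exclusion, stated for one arm, with no planned analysis that would reveal or correct its effect. Because it is stated outright, it is not a detail left to an unseen analysis plan.

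It would be too strong to conclude that the primary estimate is bound to be biased, or biased towards PGAP. The rule opens the comparison to selection; how far, and in which direction, depends on a count and a gap that the document does not give. On an assumed gap of 2 to 4 points, the shift is about 0.03 to 0.13 Roland-Morris points if 2% to 3% of controls are affected, which is plausible given the scarcity of services, and 0.1 to 0.6 points if 5% to 15% are. The power loss is minor. The case for change rests on the validity of the comparison and the ease of repair, not on a demonstrated large bias.

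**What to change.** Replace the exclusion sentence in the Control condition section with a rule that all randomised participants are analysed in their allocated arm, in the primary and the economic analyses, using all outcomes collected.

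Report uptake of other psychological pain programmes in both arms. The Client Service Receipt Inventory already records health service use for all patients at baseline, post-treatment and follow-up; it should be confirmed that its items identify such programmes and place them before or after the 10-week assessment.

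If the effect in the absence of such programmes is of interest, present it only as a labelled sensitivity analysis applied to both arms. It could either exclude these patients or set their outcomes after enrolment to missing and impute them; the second keeps outcomes measured before enrolment.

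The cost is a change of analysis wording and a short table of uptake. The downside is a possible slight dilution of the estimated effect if some controls benefit from another programme. The Trial status section reports follow-up still being collected, so the change could be made before analysis.
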